## Abstract

**Background:**

Abnormalities of vital signs are quantified by comparison with normal ranges, which are those observed in resting healthy populations. It might be more appropriate to compare the vital sign values of an individual in distress with their own usual values recorded when they were stable and well. Sensors from smartwatches or smartphones might make this possible at scale, but the proportion of patients using them is not known.

**Objective:**

This study aimed to assess the feasibility of using heart rate and mobility data from patients’ own wearable sensors as part of clinical assessments at the time of presentation to hospitals with medical emergencies, and to quantify the difference between heart rate and the change in daily steps taken by the patient on admission to acute care compared with the previously recorded values at home.

**Methods:**

This is an international, multicenter observational study using the flashmob research design. The study will recruit patients aged 18 years and older who present to emergency departments, acute medical departments, or ambulatory emergency care with an acute medical complaint. Main end points of the study include the proportion of patients assessed for an acute complaint who use wearable devices to record vital signs. The study will describe the population that uses devices that collect vital signs in terms of sex, age group, digital literacy, and the severity of illness on presentation (as measured by a standard set of vital signs and frailty). Trends in heart rate and step counts measured in the month before presentation to acute care services will be reported according to discharge or admission status. Data will be collected during a pilot phase and during a single week in centers across Europe.

**Results:**

The study has been registered and passed the required approvals in the Netherlands Medical Ethics Committee (MEC-2022-0795) and the United Kingdom Integrated Research Application System (IRAS 321129). Based on the results of a pilot study performed at a single site in the United Kingdom, a flashmob study has been concluded in hospitals throughout Europe in May 2024 and reported in 2025.

**Conclusions:**

With the increasing availability of consumer held devices able to record medically relevant information this study will provide information about the availability of these data for clinical use in a number of European settings.

**International Registered Report Identifier (IRRID):**

DERR1-10.2196/55975

## Introduction

### Background

The decision about the need of an individual to require hospital admission relies on the assessment of patients’ symptoms, signs, past medical history, medication use, diagnosis, social support at home [1-3], and a judgment about the severity of illness based on estimated risk of deterioration in the subsequent hours and days [4].

Abnormalities of vital signs are quantified by comparison with normal measurements on healthy individuals recorded during periods of physiological stability. Within these individuals, the normal measurements vary and are influenced by age, sex, body composition, medication use, and physical condition [5-7]. There is a relation between the size of change from a physiologically normal range and the number of vital signs affected by abnormality and the frequency of adverse events [8]. Abnormality might be scored with generic tools that can be applied to the majority of patients, such as the National Early Warning Score [9], or tools that are disease-specific, such as the CURB65 [10], Blatchford [11], and DECAF (Dyspnea, Eosinopenia Consolidation, Acidemia, and Atrial Fibrillation) [12]. However, these scores can under- or overestimate risk in individual patients [13].

Knowing the values of an individual patient’s vital signs while well might help clinicians to better understand and interpret their changes or trends [14], their relative degree of deviation from the patient’s own normal and get a better estimate of their personal severity of illness. Similarly, mobility has been suggested to be a vital sign [15] and could be easily quantified by step counts. Normal mobility has been shown to be a protective factor [15]. Therefore, the assessment and comparison of step count during illness might be of value.

The general public are increasingly using devices such as smartwatches and mobile telephones that can potentially measure and record vital signs such as heart rate, heart rhythm, and oxygen saturation. Currently, approximately 90% of the population in the United States [16] and 94% in the United Kingdom [17] are smartphone users. Vital signs are also increasingly being recorded at home using conventional sphygmomanometers and pulse oximeters, and these values, if recorded, might also be available.

The aim of this study is to assess the feasibility of using a patient as their own reference for vital signs by assessing the difference between vital signs on admission to acute care with their own vital sign values recorded by his or her wearable device when they are at home and well (Textbox 1).

### Objectives

The primary and secondary study objectives are described in Textbox 1.

Primary and secondary objectives.
**Primary objectives**
To assess the feasibility of using data from patients’ own wearable sensors for assessments in acute care. Feasibility will be assessed by eligibility, recruitment, retention rates, and patients’ acceptability.
**Secondary objectives**
To explore the proportion of patients assessed for an acute complaint who are wearing or carrying a device that collects data on vital signs (eg, smartwatch or other wearables).To describe the population who wear or carry devices that collect data on vital signs.To quantify the change in heart rate in patients admitted to acute care between measurements taken on presentation and previously recorded vital signs by a consumer-grade wearable while patients were stable and well.To quantify the change in step count in patients admitted to acute care between measurements taken shortly before presentation and previously recorded step counts by a consumer-grade wearable while patients were stable and well.To explore the association between trends in in vital signs with the disposition of patients (admission to a general ward, critical care area, or discharge home within 24 hours from assessment).

## Methods

### Study Design

A pilot study was performed at a single site in the United Kingdom to develop and test procedures for data collection and reporting during the previous 6 months. Based on the learning from this pilot a prospective, international, multicenter, observational study using the flashmob research design will be conducted [18]. Participating units will collect data from patients presenting with acute medical emergencies to emergency departments, acute medical units, and ambulatory emergency care. There will be no randomization, blinding, and treatment allocation.

### Population

Patients who present at the emergency department, acute medical department, and ambulatory emergency care unit in secondary and tertiary hospitals in a sample of hospitals in the Netherlands, United Kingdom, Denmark, and Switzerland with an acute medical complaint. Acute medical complaints are nonsurgical admissions commonly treated by internists such as acute physicians, cardiologists, pulmonologists, gastroenterologists, endocrinologists, geriatricians, and similar (Textbox 2).

Inclusion and exclusion criteria.
**Inclusion criteria**
Participants in this study must be able to give informed consent, have an acute presenting complaint, be aged 18 years or older, and use any of the following: smartwatch, activity tracker, or other wearable monitoring devices, or a smartphone that collects step counts or data from other wearable devices.
**Exclusion criteria**
Patients who are unable to give informed consent or endure an imminently life-threatening illness.
**Main study end point**
To quantify the proportion of patients assessed for an acute complaint who are wearing a device that collects data on vital signs (ie, heart rate and step count).
**Secondary study end points**
Secondary end points will focus on four areas of interest:The difference between the heart rate at rest from the wearable device 24 hours, 1 week, and 1 month before assessment by emergency practitioners compared with the first set of vital sign parameters measured on admission to acute care.The change in daily steps taken in the month before admission to acute care.To describe the population that is wearing devices that collect data on vital signs in terms of gender, age group, severity of illness as measured by a standard set of vital signs, level of education, and digital literacy and frailty.To explore the association of changes in heart rate from the community to assessment in acute care services with clinical end points such as admission to a general ward or admission to a critical care area or discharge home within 24 hours from the time of clinical assessment.

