Data items were collected as part of the "Feasibility of Using resting heart rate and step counts from patient-held Sensors during clinical assessment of medical Emergencies" (FUSE) study.Site ID is the unique number for each site.Participant ID is a consecutive number (no identifiable information is collected).Location is the location where the patient is included in the study (ie, emergency department, medical admissions unit, ambulatory emergency care, or other).Sex as reported by the patient (ie, men, women nonbinary, or unknown).Date of birth, which will be used to compute an age category.Date and time of first presentation, defined as the time that a patient presents at the location.Highest level of education is the patient finished highest level of education or the level of education the patient is currently following (ie, primary school, secondary school, and higher education).Digital literacy is assessed using 2 questions asking for confidence of using the internet and confidence of using mobile apps, which patients can answer using a 5-point Likert scale.Device is the device used to measure heart rate, and the brand and type will be recorded.Phone is the phone that patients use, and this will be used to retrieve the step count and heart rate data. The brand and type will be recorded.Heart rate on the device is the heart rate that is stored and measured by the device, and the resting heart rate (as presented by the device), the minimum, maximum, and mean or median (depending on the device) will be retrieved on three-time points, namely on presentation, within 24 hours before presentation and within 1 week (plus or minus 1 day) before presentation.Walking distance is the number of steps of exact distance (in kilometers or miles), either measured by the device of the phone. The daily walking distance of the 7 days before the presentation will be recorded.Frailty as quantified through the Clinical Frailty Scale [19].Mobility will be assessed as either normal or impaired. Mobility is considered impaired if the patient is unable to get onto the bed unaided, either from the ambulance gurney or whichever way they arrive.Date and time of the first set of vital signs is defined as the time that the first set of vital signs are measured.Heart rate on admission is the first heart rate measured during clinical examination.National Early Warning Score [9] as a standardized assessment of the severity of illness, based on the first full measurements of respiratory rate (per minute), oxygen saturation (in %), temperature (in °C), heart rate (per minute), systolic blood pressure (in mm Hg), AVPU (alert, verbal, pain, and unresponsive) score, and the use of any supplemental oxygen.Outcome is assessed at midday on the day after the initial assessment and can be (ie, discharged, admitted to hospital, admitted to high care or intensive care, or deceased).

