### Limitations

The distribution of wearables in the population might point toward the exclusion of a significant proportion of the population from this type of support: patients who are less financially well off or not sufficiently digitally or health literate might be disadvantaged in a future health care. This data will hence be collected as part of FUSE. While this study focuses on readily available data and will require in future supplementation by detailed qualitative data.

The study is conducted by a group of secondary care clinicians with expertise in medical emergencies. Many of the patients who will be screened and included will have previously presented in primary care. There is no theoretical reason that the results from this study might not be applicable to those presenting in primary care, but this might require future research.

In preparation of the study, we reviewed sales for the top 20 devices in the Dutch and British markets. For these devices, we have created a data dictionary for investigators that will enable them to assist patients in the location of relevant data. With new devices coming online and changes in consumer habits, the frequency distribution of these devices might however be soon outdated.

The study will explicitly not address the quality of data collected in wearables. We will, however, report on the distribution of devices and approval for medical use where applicable. In the same vein, we anticipate that the duration of usage by individuals will affect the measurements. This is something that we might not be able to evaluate in the current setup.

Given that patients will use a range of devices with different methods for data acquisition and different usage patterns our analysis will focus on the comparison of relative changes in parameters for individuals (intraindividual variation). This relies on the assumption that individuals will have a pattern of usage that is constant over time. Further research will be required, especially if it turns out that the variation between the collected parameters turns out to be large in the days before deterioration and presentation to the hospital.

Finally, future health care needs to be equitable. FUSE will include data that will allow us to gauge some aspects of equity, diversity, and inclusion which are crucial for the development of policy and strategy in this field.

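### The secondary heart-rate change sets a wearable value at home against a clinical spot reading on arrival, so the average change carries an instrument-and-metric offset of unknown size; a same-device contrast should be reported beside it.

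*Protocol article*

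**What the plan says.** The Protocol article, Secondary study end points (Textbox 2), defines the home side as "The difference between the heart rate at rest from the wearable device 24 hours, 1 week, and 1 month before assessment by emergency practitioners" and the arrival side by "compared with the first set of vital sign parameters measured on admission to acute care". Secondary Outcome Measures repeats the contrast as an absolute and a proportional change, but calls the home value heart rate at home without the restriction to rest.

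The data item list under Study Procedures (Textbox 3) fixes the arrival value: "Heart rate on admission is the first heart rate measured during clinical examination". It states no rest condition. For the wearable, the same list says "the resting heart rate (as presented by the device), the minimum, maximum, and mean or median (depending on the device) will be retrieved", at three time points: "namely on presentation, within 24 hours before presentation and within 1 week (plus or minus 1 day) before presentation". A device reading at presentation is thus collected, but neither the end point nor the outcome definition names it as the arrival value.

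Limitations acknowledges that devices acquire data differently and answers that "our analysis will focus on the comparison of relative changes in parameters for individuals". It adds that the quality of wearable data will not be addressed. Data Analysis relates absolute and proportional change to the clinical end points by regression.

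**The concern.** A device's resting rate is its own summary of quiet periods. The first rate at clinical examination is one reading, by other means, soon after arrival. Subtracting one from the other mixes two things: how far the patient has moved from their own normal, and how far the two measures would differ in a patient who had not moved at all.

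The secondary objective is to quantify change from the stable state, and the Discussion expects clinicians to be reassured when vital signs have not changed. An offset bears directly on both. It does not shrink with sample size. The stated protection, comparing each person with themselves, works only when the same measure stands at both ends.

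**Working it through.** No figure in the plan is in dispute, so there is nothing to reproduce. The check compares the definitions and then illustrates the size.

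**Model.** For one patient, let H be the device value at home, d the true rise by arrival, and b the clinic spot rate minus the device rate in the same physiological state.

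- Clinic value on arrival: H + d + b.
- Planned absolute change: (H + d + b) − H = d + b.
- Planned proportional change: (d + b)/H.

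H cancels from the absolute change because it belongs to the person. b does not, because the switch of measure occurs within the person.

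**Admitted versus discharged.** If the mean of b is equal in both groups, it cancels from the difference in mean absolute change. It need not cancel from proportional change, because b is divided by H. With b = 10 bpm and home rates of 60 and 70 bpm (all assumed), b/H is 10/60 = 16.7% and 10/70 = 14.3%, a gap of 2.4 percentage points without any difference in d.

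**Illustration with d = 0.** The documents give neither b nor the SD of the paired difference, so both are assumptions. n = 209 is the number under Results with data on at least 2 collection points; it may not be the number with this particular contrast. SE = SD/√209, and the test is a two-sided 5% normal test on the paired difference. The last three columns give the probability of declaring a change when there is none.

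| b (bpm) | b/65 | SD 10 (SE 0.69) | SD 15 (SE 1.04) | SD 20 (SE 1.38) |
|---|---|---|---|---|
| 0 | 0% | 0.05 | 0.05 | 0.05 |
| 2 | 3.1% | 0.82 | 0.49 | 0.30 |
| 5 | 7.7% | 1.00 | 0.998 | 0.95 |
| 10 | 15.4% | 1.00 | 1.00 | 1.00 |

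For example, b = 5 with SD 15 gives 5/1.04, or z = 4.82 with the unrounded SE.

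**What the presentation reading can do.** Suppose the device value at presentation reflects a share w of the acute rise (0 ≤ w ≤ 1), with w < 1 if it is a daily summary that includes hours before arrival.

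- Device-to-device change: (H + w·d) − H = w·d. It is free of b, but diluted if w < 1.
- Device at presentation minus clinic: (H + w·d) − (H + d + b) = −[b + (1 − w)·d]. It isolates b only if w = 1.

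If d and b are both non-negative, w·d ≤ d ≤ d + b, so the two contrasts bracket the true rise. Neither alone identifies it.

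**Time points.** The data item list supports the device-to-device contrast at 24 hours and 1 week. It lists no device heart rate at 1 month.

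**The case against.** The strongest reply is that the cross-instrument comparison is the study's question. The aim at the end of the Introduction's Background sets vital signs on admission against the patient's own wearable values. The admission rate is also an input to the early warning score on the data item list. This stands: replacing the planned contrast would change the question, so the device contrast belongs beside it.

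A within-device comparison may already be intended. Data Analysis compares heart rate across time points without naming the source, and the secondary objective speaks of readings at presentation without naming an instrument. A separate analysis plan, not shown here, could settle it. But the end point and outcome definitions both name the first clinical vital signs, and nothing in the article assigns the device presentation reading to this contrast.

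Several stronger readings are tempting and not supported:

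- *The home metric is left open between resting, mean and median.* Textbox 2 fixes the resting rate. In the data item list the device-dependent choice concerns mean or median, and resting rate is a separate item. Only the looser wording in Secondary Outcome Measures blurs this.
- *The patient's different state on arrival is artefact.* Much of it is the signal the study seeks. Only instrument, metric and arousal unrelated to illness could be artefact.
- *Every patient will show a false rise.* No document gives the size or sign of the offset.
- *The association with disposition is invalidated.* A common offset cancels from the difference in absolute change. Variation in the offset between devices would add noise to the predictor, by an unknown amount.

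The stakes are also limited: this is a secondary end point of a feasibility study.

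**Conclusion.** The point holds in a limited form. As defined, the average heart-rate change is true change plus an offset from switching instrument and metric, and intraindividual comparison does not remove it. The size cannot be derived from the documents. Over the assumed range of 0 to 10 bpm on 65 bpm, the added change runs from 0% to 15.4%. With 209 patients, an assumed 5 bpm offset would almost always be declared a change (probability 0.95 or more for SDs of 10 to 20 bpm).

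The exposure is in the average absolute and proportional change. The admitted-versus-discharged difference in absolute change is protected if the offset is equal in the two groups; proportional change is not generally protected. The proportion of patients with devices is unaffected.

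A reader might conclude that the planned contrast should be abandoned, or that the presentation readings yield the offset directly. The first conflicts with the declared aim. The second fails if a device's resting rate at presentation is a daily summary. The conclusion is therefore a worthwhile, inexpensive addition to the analysis.

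**What to change.** 1. Keep the planned contrast of home device versus first clinical reading, and label it as cross-instrument wherever it is reported. Use the same description of the home value (resting) in Textbox 2 and in Secondary Outcome Measures.
2. Add a pre-specified, co-reported device-to-device contrast: presentation versus 24 hours and versus 1 week, with the same metric at both ends in the same patient. Show results by metric type and do not mix metrics within a patient.
3. Report the paired difference, device at presentation minus clinic, as a descriptive agreement check. State that it mixes offset with any dilution of an acute rise, and do not use it to correct the planned contrast.
4. State under Limitations that comparing each person with themselves does not remove the switch from device to clinic.

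**Cost.** Analysis wording and a few extra tables; the 24-hour, 1-week and presentation readings are already on the data item list. Patients without a device reading at presentation are missing from the added contrast, so report its denominator. It cannot cover 1 month, because no device heart rate is listed for that time. Results describes data collection that has already taken place, so any addition made after the data were analysed should be labelled as such.

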### Study Procedures

All patients aged 18 years and older who present to acute care will be asked if they wear a smartwatch, activity tracker, or wearable that measures heart rate.

Patients will be asked to give informed consent in line with the guidance from the participating countries. This is likely to include written informed consent in the Netherlands, Denmark, and the United Kingdom. Informed consent will be explicit about accessing data from patient-held wearables (Multimedia Appendix 1). Once consent has been obtained, initial data will be entered into the case report form, and the remaining items of the case report form will be completed on the day after the initial presentation or later (Textbox 3). Study documentation will include a guide for investigators to interrogate commonly used wearable devices (Multimedia Appendix 2). Parameters recorded will vary according to the different devices used but should at least include heart rate and step count.

Data items were collected as part of the "Feasibility of Using resting heart rate and step counts from patient-held Sensors during clinical assessment of medical Emergencies" (FUSE) study.Site ID is the unique number for each site.Participant ID is a consecutive number (no identifiable information is collected).Location is the location where the patient is included in the study (ie, emergency department, medical admissions unit, ambulatory emergency care, or other).Sex as reported by the patient (ie, men, women nonbinary, or unknown).Date of birth, which will be used to compute an age category.Date and time of first presentation, defined as the time that a patient presents at the location.Highest level of education is the patient finished highest level of education or the level of education the patient is currently following (ie, primary school, secondary school, and higher education).Digital literacy is assessed using 2 questions asking for confidence of using the internet and confidence of using mobile apps, which patients can answer using a 5-point Likert scale.Device is the device used to measure heart rate, and the brand and type will be recorded.Phone is the phone that patients use, and this will be used to retrieve the step count and heart rate data. The brand and type will be recorded.Heart rate on the device is the heart rate that is stored and measured by the device, and the resting heart rate (as presented by the device), the minimum, maximum, and mean or median (depending on the device) will be retrieved on three-time points, namely on presentation, within 24 hours before presentation and within 1 week (plus or minus 1 day) before presentation.Walking distance is the number of steps of exact distance (in kilometers or miles), either measured by the device of the phone. The daily walking distance of the 7 days before the presentation will be recorded.Frailty as quantified through the Clinical Frailty Scale [19].Mobility will be assessed as either normal or impaired. Mobility is considered impaired if the patient is unable to get onto the bed unaided, either from the ambulance gurney or whichever way they arrive.Date and time of the first set of vital signs is defined as the time that the first set of vital signs are measured.Heart rate on admission is the first heart rate measured during clinical examination.National Early Warning Score [9] as a standardized assessment of the severity of illness, based on the first full measurements of respiratory rate (per minute), oxygen saturation (in %), temperature (in °C), heart rate (per minute), systolic blood pressure (in mm Hg), AVPU (alert, verbal, pain, and unresponsive) score, and the use of any supplemental oxygen.Outcome is assessed at midday on the day after the initial assessment and can be (ie, discharged, admitted to hospital, admitted to high care or intensive care, or deceased).

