#### Recruitment and Consent

Patients eligible for inclusion are asked if they use a smartwatch or other wearables that measure heart rate by a collaborator of the study. If they do they fulfill the inclusion criteria, and they will then be informed about the study procedures and asked to participate after they have read the patient information form. After receiving this form patients will be asked if they will agree to sign written informed consent.

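### The inclusion criteria admit patients whose only device is a step-counting smartphone, but the screening question asks only about wearables, and the device proportion is worded inconsistently

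*Protocol article*

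**What the plan says.** The inclusion criteria (Textbox 2) let a patient qualify through any one of several devices. The list ends "or a smartphone that collects step counts or data from other wearable devices", so a phone that counts steps is enough by itself.

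Screening is described twice. Study Procedures says that all adults presenting to acute care "will be asked if they wear a smartwatch, activity tracker, or wearable that measures heart rate". Recruitment and Consent says: "Patients eligible for inclusion are asked if they use a smartwatch or other wearables that measure heart rate by a collaborator of the study". It continues: "If they do they fulfill the inclusion criteria, and they will then be informed about the study procedures". Neither section contains a question about phones.

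The device proportion appears in several places:
- The main study end point counts patients who wear a device giving heart rate and step count.
- The secondary objectives count the "proportion of patients assessed for an acute complaint who are wearing or carrying a device that collects data on vital signs".
- Secondary Outcome Measures also describes the population that wears or carries devices.
- Primary Outcome Measures refers to eligible patients who have devices, without saying which devices or whether they must be worn.

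The case report form has separate Device and Phone items. Study Procedures has the form filled in once consent is given.

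**The concern.** How common usable devices are among acute medical patients is the central quantity of this descriptive study. It needs one case definition, and a screening question that can find every patient who meets it. Here the eligibility rule is wider than the question used to apply it. A patient with a phone and no wearable meets the criteria, answers no at screening, and is handled like a patient with no device at all.

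Three things are at stake. A reader cannot tell whether the reported proportion describes wearables or any device. Step-count change is a secondary end point and phones are an accepted source of steps, so usable step data would be lost. The article also wants to learn who is left out of this kind of monitoring, and that question is blurred if phone owners without a wearable are grouped with patients who own nothing.

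**Working it through.** **Comparison of the texts.** The main check is to ask, at each place, what happens to a patient whose only device is a step-counting phone.

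| Place in the protocol article | Device that counts | Phone-only patient |
|---|---|---|
| Inclusion criteria | watch, tracker, other wearable, or step-counting phone | Eligible |
| Study Procedures, screening question | worn devices, with heart rate | Not asked about |
| Recruitment and Consent | watch or other heart-rate wearable | Not asked about; no other route given |
| Study Procedures, minimum data | heart rate and step count | May not meet the minimum |
| Abstract, Methods | wearables used to record vital signs | Not counted on a plain reading |
| Main study end point | worn device giving heart rate and steps | Not counted on a plain reading |
| Secondary objectives; Secondary Outcome Measures | worn or carried device | Counted, if a phone is a carried device |
| Primary Outcome Measures | device, type not stated | Undetermined |

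The first three rows cannot all be followed for this patient. The Phone item on the case report form does not resolve this, because the form is started only after consent and so after the screening question has been answered.

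**Planned size.** The article's only planned figure reproduces: 40 hospitals × 50 patients = 2000 screened. The largest 95% half-width for a proportion at that size is 1.96 × √(0.25/2000) = 0.022, or 2.2 points. It says nothing about which definition is estimated.

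**Reported counts (Results).** 1137 screened and 452 included.
- Included over screened: 452/1137 = 39.8% (Wilson 95% interval 36.9 to 42.6).
- Screened but not included: 1137 − 452 = 685.
- Largest 95% half-width at this size: 1.96 × √(0.25/1137) = 0.029, or 2.9 points.

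**How few patients would matter.** A shift of 2.9 points is 0.029 × 1137 ≈ 33 patients, and 33/685 = 4.8%. If about 33 of the 1137 screened patients were phone-only, the choice of definition would move the proportion by as much as the largest sampling margin.

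**Illustration only.** Let s be an assumed share of the 685 who hold only a step-counting phone. Adding them gives (452 + s × 685)/1137:
- s = 0.10: 520.5/1137 = 45.8%
- s = 0.50: 794.5/1137 = 69.9%
- s = 0.90: 1068.5/1137 = 94.0%

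These are not estimates. The article gives no value for s, the 452 are patients who passed consent and the exclusions, and it is not stated whether some of the 452 were themselves phone-only.

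**The case against.** The best defence is that most of the article points one way. The abstract, the main end point and both screening descriptions concern wearables. The worn-or-carried wording sits in a secondary objective and a secondary outcome, and the primary outcome's wording is unspecific rather than contradictory. On that reading the phone clause in the inclusion criteria is the outlier, and the main end point and its screening question largely agree. This stands as an account of the probable intent. It does not remove the conflict, because the clause is a current eligibility rule and nothing in the article withdraws it.

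The heart-rate qualifier in Study Procedures may attach only to the last item in its list, so a step-only activity tracker might be covered. That is fair, but a phone is not covered on either reading.

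Several stronger conclusions are tempting, and the documents do not support them:
- A reader might infer that the objective itself counts smartphones. It says "who are wearing or carrying a device that collects data on vital signs" and its example is a smartwatch or other wearable. A phone is a reasonable inference, since the Background treats mobile phones as potential vital-sign recorders, but only the inclusion criteria make a phone alone sufficient.
- A reader might infer that sites applied different rules and that the results mix them. That is a risk created by the text. No section reports it, and the two screening descriptions agree with each other.
- A reader might infer that phone-only patients are the largest group, because "approximately 90% of the population in the United States [16] and 94% in the United Kingdom [17] are smartphone users". Those figures cover all smartphone users, including those who also wear a device, in general populations.
- A reader might subtract 39.8% from 90% or 94% and report a gap of about 50 to 54 points. That sets a post-consent inclusion fraction against general-population phone ownership, so it does not measure the difference between the two definitions.

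**Conclusion.** The concern holds as an internal inconsistency. Phone-only patients are eligible under the inclusion criteria and would be missed by the screening procedure as written, and the device proportion has no single definition across the objectives, end points and outcome measures. This rests on the text alone and needs no assumption.

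The size of the effect is unknown. It would equal the largest sampling margin if about 33 of the 1137 screened patients were phone-only, but the article does not say how many there were, and no corrected proportion can be calculated. The 39.8% should be read as the inclusion fraction and nothing more. The definition needs to be settled for any reported device proportion to be interpretable. Because the study is descriptive, with no hypothesis test described for this proportion, the consequence is one of meaning and not of error rates.

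**What to change.** **Wording.** Use one device definition, with wearable and phone-only as named categories, in the inclusion criteria, main end point, secondary objectives, Study Procedures, Recruitment and Consent, and the primary and secondary outcome measures.

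**Any further use of the protocol.** Ask every screened patient two yes/no questions: whether they use a wearable that records heart rate, and whether they have a smartphone that records steps. Recruit on either, as the inclusion criteria say. Report two pre-specified proportions over all screened patients: wearable (primary, matching the main end point) and any device including phone only (secondary, matching the worn-or-carried objective). All screened patients are the right denominator because having a device is itself a condition of eligibility. Restrict heart-rate analyses to patients with heart-rate data, and use both groups for steps. The cost is one extra screening item, aligned wording, and some additional step-only records.

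**Data already collected.** The abstract says the flashmob study concluded in May 2024, so the added question cannot help these patients. State which rule the sites applied. Classify the included patients by the Device and Phone fields, and report wearable and phone-only patients separately. Do not present included over screened as the any-device proportion. The cost is a reclassification of fields already on the form and a query to sites. It cannot recover phone-only patients who were turned away at screening, and the report should say so.
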